### Statistical methods

The detailed contents of the statistical analysis methods of this clinical trial are as follows.

#### Data set category

Intention-to-treat (ITT): No one was excluded from the main analysis set after randomizationPer-protocol set (PPS): Good compliance case data that meets the main inclusion and exclusion criteria without affecting the main curative effects of prohibiting drugs within the next 24 weeksSafety set (SS): Case data involving usage of the investigational drug product at least once, including safety evaluation

#### Statistical analysis technique

The number of participants selected and completing follow-up visits in the population and centers will be listed separately, and the three analysis data sets (ITT, PPS, SS) as specified above will be identified [14]. Cases of protocol violation should also be listed and the reasons indicated. In terms of outcome indicator analysis, continuous variable indicators will count the number of cases (*n*), mean ($$ \overline{x} $$), standard deviation (*SMD*), median (*M*), minimum (*min*), and maximum (*max*). The difference between groups will be analyzed using Student’s *t*-test. Counting and grading data will be used to calculate the frequency and composition ratio. The *χ*^2^ test/chi-square test will be used for differences between groups. Unless otherwise stated, all statistical tests will be conducted in a bilateral manner. For example, if *P* ≤ 0.05, the difference between groups is statistically significant. Results of this clinical trial will be analyzed using SAS version 9.2 or above software.

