### Trial design

This study is a multicenter, parallel controlled, randomized, open clinical trial (version 1.1; date 11 Dec. 2019, phase IV post-marketing) in China, which has been registered with the Chinese Clinical Trial Registry (http://www.chictr.org.cn/index.aspx) on March 23, 2020. The trial registration number is ChiCTR2000031166. The detailed flowchart is shown in Fig. 1. All eligible participants will be randomly divided into two groups in a 1:1 ratio: experimental group [conventional drug (erythropoietin) therapy+ iron polysaccharide complex] and control group [conventional drug (erythropoietin) therapy + iron sucrose injection]. Participants will complete the study visit at baseline (within 7 days before the first treatment) and weeks 4, 8, 12, 16, 20, and 24 after the first treatment. We used the SPIRIT reporting guidelines [11] in the current study.

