### Sample size

This clinical trial set has a non-inferiority threshold of 7 (%) and a variance of 11 (%) for the positive control group. We predict a 2% real difference between the tested drug and positive control in transferrin saturation. The unilateral significance level is 2.5%, with an assurance of 80%. In the case of a 1:1 sample size between the control group and the experimental group, a total of 154 samples will be collected (77 of which will be in the control group and the experimental group, respectively). Considering a 20% drop-out rate, the actual planned inclusion number will be 186 cases.

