### Endpoints

#### Primary endpoint

TSAT will be measured at 12 weeks after baseline treatment.

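### Week-12 TSAT is compared by an unadjusted t-test although every randomised participant has a baseline TSAT; a pre-specified ANCOVA would use it at the cost of one degree of freedom

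*Protocol article*

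**What the plan says.** Primary endpoint (protocol article): "TSAT will be measured at 12 weeks after baseline treatment". This is the value at week 12, not a change from baseline.

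Statistical analysis technique, on continuous outcomes: "The difference between groups will be analyzed using Student"; the sentence goes on to name the t-test. No covariate or baseline adjustment is mentioned. The same section adds: "Unless otherwise stated, all statistical tests will be conducted in a bilateral manner".

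Baseline TSAT will exist for everyone randomised. It is an inclusion criterion (above 20% and below 50%), Setting and recruitment has eligibility confirmed again after two weeks of iron sucrose, and Trial design schedules a baseline assessment: "Participants will complete the study visit at baseline (within 7 days before the first treatment").

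Sample size gives a "non-inferiority threshold of 7" (%), "a variance of 11 (%) for the positive control group", and then: "We predict a 2% real difference between the tested drug and positive control in transferrin saturation". On error rates: "The unilateral significance level is 2.5%, with an assurance of 80"%. The result is 77 evaluable per arm, 154 in all, raised to 186 for 20% drop-out. No correlation between baseline and week-12 TSAT enters the calculation.

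**The concern.** The trial's conclusion turns on where a confidence limit falls relative to a 7-point margin. Its width depends on the error variance. If baseline TSAT predicts week-12 TSAT to any useful degree, an unadjusted comparison leaves in the error term variation that a covariate already collected would remove. The interval is then wider than it need be, and a drug that is truly non-inferior is more likely to miss the margin. Because the protocol names the t-test rather than leaving the method open, the choice itself can be assessed. Adjustment also has to be fixed before the data are seen, since a covariate chosen afterwards would carry less weight.

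**Working it through.** **Inputs.** Margin 7, assumed true difference 2, the figure 11, one-sided level 2.5%, power 80%, 1:1 allocation, 77 per arm, 186 enrolled and 20% drop-out, all from Sample size. The correlation r is not in the document and is varied from 0 to 0.7.

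**1. Reproduce the plan's figure.** The 2-point difference is taken as being against the test drug, so the distance to the margin is 7 − 2 = 5. By the normal approximation, n per arm = 2(1.960 + 0.842)² × SD² / 5².

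- With 11 as a standard deviation: 2 × 7.849 × 121 / 25 = 75.98, so 76 per arm (152).
- With 11 as a variance: 2 × 7.849 × 11 / 25 = 6.9, so 7 per arm, which is far from the plan.

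The 11 is therefore a standard deviation. By the noncentral t distribution, 76 per arm gives 79.5% power and 77 gives 80.0%. The stated 77 reproduces exactly, with the raw SD and no correlation term. The trial was sized for an unadjusted comparison.

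**2. Evaluable number after drop-out.** 154 × 1.2 = 184.8 (77 × 1.2 = 92.4, or 93 per arm), which gives 186. Losing 20% of 186 leaves 186 × 0.8 = 148.8, about 74 per arm. Dividing instead, 154 / 0.8 = 192.5, would call for 193. At 74 per arm the unadjusted t-test has 78.4% power. This small shortfall comes from the inflation method, not from the test.

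**3. Add baseline TSAT as a covariate.** Residual SD = 11√(1 − r²). Standard error = residual SD × √(2/n). Degrees of freedom = 2n − 3, one fewer than for the t-test. Power is from the noncentral t with noncentrality 5 / standard error.

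| r (assumed) | Residual SD | SE, n = 77 | 95% CI half-width, n = 77 | Power, n = 77 | Power, n = 74 |
|---|---|---|---|---|---|
| 0 | 11.00 | 1.77 | 3.50 | 80.0% | 78.4% |
| 0.2 | 10.78 | 1.74 | 3.43 | 81.6% | 80.0% |
| 0.3 | 10.49 | 1.69 | 3.34 | 83.6% | 82.1% |
| 0.5 | 9.53 | 1.54 | 3.03 | 89.9% | 88.7% |
| 0.7 | 7.86 | 1.27 | 2.50 | 97.5% | 97.0% |

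The r = 0 row is the worst case: to one decimal place, giving up one degree of freedom leaves power unchanged. At 74 per arm, r of about 0.20 brings power back to 80%.

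**4. How the entry window bears on r.** Restricting baseline TSAT to 20–50% tends to lower r. As an illustration, assume unrestricted TSAT is normal with mean 30 and SD 11 (the mean is not in the document). Truncation then gives SD 7.46, so u = 7.46 / 11 = 0.678. The restricted correlation is r·u / √(1 − r² + r²u²), which takes 0.3, 0.5 and 0.7 to about 0.21, 0.36 and 0.55.

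**The case against.** The strongest reply is that nothing here is an error. In a randomised trial the unadjusted t-test is valid and unbiased, and here it matches the sample size. A reader might infer that power has been lost and that adjustment would restore it. The documents do not support that: 77 per arm delivers the planned 80%, and the dip to 78.4% at 74 per arm arises from drop-out inflation. This part of the reply stands in full.

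It also stands that the benefit rests on a correlation the document does not supply. The entry window, the TSAT-triggered iron changes (Dose adjustment) and the exit rule for persistently low TSAT (Withdrawal and drop-out) could all weaken it. At r = 0.2 the gain at 77 per arm is only 1.6 points.

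A second tempting reading is that chance baseline imbalance is a further harm beyond the wider interval. It is not: the t-test's standard error already allows for such imbalance, so counting both would count one thing twice. The size of any shift would also depend on the baseline SD, which the document does not give.

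Third, one might argue that nine centres oblige the model to carry a centre term. Randomization and allocation mentions no stratification by centre, and no centre effect can be quantified from the document.

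Finally, an analysis plan that is not shown may already name covariates. If so, this section should be brought into line with it. The article does more than stay silent, since it names a specific method, and a better one is available from the same data.

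**Conclusion.** The point holds as a free improvement, not as a flaw that undermines the design. The stated test is valid and adequately matched to 77 per arm; what is forgone is precision. At 77 per arm the gain over 80.0% is 1.6 points at r = 0.2, 3.6 at 0.3, 9.9 at 0.5 and 17.5 at 0.7, and nothing at r = 0. The lower part of this range deserves more weight because of the entry window. The figures assume SD 11, a true difference of 2 against the test drug, a linear relation with a common slope in both arms, and one-sided 2.5%.

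One related matter is independent of covariates. Sample size is built on non-inferiority with a margin, whereas Statistical analysis technique describes two-sided tests of difference at P ≤ 0.05 and no comparison with that margin. Changing the test to ANCOVA does not cure this by itself; the interval has to be set against the margin explicitly.

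**What to change.** State the primary analysis as an ANCOVA of week-12 TSAT on treatment and baseline TSAT, fixed before the data are examined. Report the adjusted difference (test minus control) with its two-sided 95% confidence interval, and conclude non-inferiority if the lower limit lies above −7. Define which TSAT measurement is the baseline; the one taken after the two-week iron sucrose run-in and before first treatment is the natural choice. Keep the unadjusted t-test as a sensitivity analysis.

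The same adjustment can be applied to continuous secondary endpoints measured at baseline, such as Hb, SF, Hct, HsCRP, EQ5D-5L and the oxidative-stress markers. Secondary endpoints words these as changes between groups, which may mean change from baseline, so the text should say which is intended. A centre term is optional.

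The cost is a change of wording and one degree of freedom (eight more if nine centres are included). No participants, visits or assays are added, and the sample size can stay as it is.

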There is little domestic clinical evidence of iron polysaccharide complex in the treatment of CKD-related anemia, so the application value and advantages of iron polysaccharide complex in the treatment of anemia in maintenance hemodialysis patients cannot be fully confirmed [19, 20]. Therefore, it is necessary to carry out further clinical trials to clarify the efficacy and safety of iron polysaccharide complex in correcting anemia in the maintenance of hemodialysis participants. In this study, intravenous injection of iron agent—iron sucrose will be used as the control group, and it is assumed that the efficacy and safety of iron polysaccharide complex in anemia and in maintenance hemodialysis participants will be non-inferior to that of iron sucrose injection. The purpose of this study is to increase the head-to-head data of oral iron compared with intravenous iron treatment and provide high-quality theoretical support for the treatment of CKD participants with CKD-related anemia. It is expected that this clinical trial will provide strong evidence as to the safety level and efficacy of iron polysaccharide complex in the treatment of anemia in maintenance hemodialysis participants. This study will provide a stronger evidence base for the development of guidelines in the treatment of CKD-related anemia and the establishment of efficacious and safe alternative treatments for managing iron deficiency anemia in chronic hemodialysis patients.

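### The trial is sized for non-inferiority with a 7-point TSAT margin, but the stated analysis is a two-sided t-test of no difference, which cannot show non-inferiority

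*Protocol article*

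**What the plan says.** The Sample size section of the protocol article sets up a non-inferiority design: "This clinical trial set has a non-inferiority threshold of 7 (%) and a variance of 11 (%) for the positive control group". It adds "We predict a 2% real difference between the tested drug and positive control in transferrin saturation" and "The unilateral significance level is 2.5%, with an assurance of 80"%. The result is 77 evaluable participants per arm, 154 in total. The Discussion gives the matching hypothesis, that the oral drug "will be non-inferior to that of iron sucrose injection". The primary endpoint is TSAT at week 12.

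Statistical methods opens by announcing that the analysis methods follow in detail. For continuous outcomes, the subsection Statistical analysis technique then says "The difference between groups will be analyzed using Student"'s t-test. It continues "Unless otherwise stated, all statistical tests will be conducted in a bilateral manner" and treats P ≤ 0.05 as a statistically significant difference between groups. A chi-square test is named for counts, which does not concern TSAT. The section has no separate rule for the primary endpoint, no confidence interval, and no reference to the 7-point margin.

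**The concern.** The two parts of the article test different null hypotheses. The design asks whether oral iron is worse than intravenous iron by 7 points or more. The stated test asks whether the two means are equal. Failing to reject equality is not evidence that the deficit is below 7 points, because imprecise data also give P > 0.05. Rejecting equality does not show that the deficit reaches 7 points, because a precise trial can detect a small, acceptable deficit.

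Followed as written, the analysis neither confirms nor refutes the trial's hypothesis. If P > 0.05 were taken as success, noise would be rewarded. If P ≤ 0.05 in favour of intravenous iron were taken as failure, a trial that met its margin could be reported as negative. The trial is open-label, so a success criterion that is left ambiguous could also be settled after the data are seen.

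**Working it through.** **Inputs.** From Sample size: margin 7, planned difference 2, one-sided alpha 2.5%, power 80%, 1:1 allocation, 77 per arm. The figure of 11 is labelled a variance, but the stated sample size is reproduced only if it is the SD. From Statistical analysis technique: two-sided t-test, P ≤ 0.05. Differences below are oral minus intravenous, and a lower TSAT on oral iron is taken as the inferior direction. SDs other than 11 are assumptions, shown as a range.

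**1. Reproduce the stated sample size.** n per arm = 2 × SD² × (z₀.₉₇₅ + z₀.₈₀)² / (margin - deficit)² = 2 × 121 × (1.960 + 0.842)² / (7 - 2)² = 76.0, so 76 by the normal approximation. With the noncentral t, 77 per arm is the first size to reach 80% (76 gives 79.5%, 77 gives 80.03%). This matches the article. Alternatives do not: a planned difference of 0 gives 39 per arm, 2 points in favour of oral iron gives 24, and SD = √11 gives 7. The number therefore comes from a non-inferiority test with SD 11 and a 2-point deficit on oral iron.

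**2. Power of the stated test.** SE = 11 × √(2/77) = 1.773. With 152 degrees of freedom the critical t is 1.976. At a true difference of -2, the two-sided t-test gives P ≤ 0.05 in 20.2% of trials and P > 0.05 in 79.8%.

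**3. Where the two rules turn.** The 95% CI half-width is h = 1.976 × SE.
- Non-inferiority: estimate - h > -7, so estimate > -7 + h.
- Oral iron not significantly worse: estimate > -h.

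The thresholds coincide only when h = 3.5. At SD 11, h = 1.976 × 1.773 = 3.50, so they do coincide, but only through this combination of SD and sample size. With all 186 planned participants analysed (93 per arm), SE = 1.613 and h = 3.18, and the thresholds are -3.82 and -3.18.

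**4. How far the rules separate, 77 per arm.**

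| SD | h | Non-inferior if estimate exceeds | Not significantly worse if estimate exceeds | P > 0.05 when the true difference is -7 |
|---|---|---|---|---|
| 9 | 2.87 | -4.13 | -2.87 | 0.2% |
| 11 | 3.50 | -3.50 | -3.50 | 2.5% |
| 13 | 4.14 | -2.86 | -4.14 | 8.7% |
| 15 | 4.78 | -2.22 | -4.78 | 18.0% |
| 16 | 5.10 | -1.90 | -5.10 | 23.0% |

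The margin test holds the error at a true difference of -7 at 2.5% for every SD in the table.

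At SD 9, an estimate between -4.13 and -2.87 meets the margin yet has P ≤ 0.05. At the planned difference of -2 this happens in about 20% of trials (20.6% when sampling variation in the SD is included).

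**5. Disagreement at a true SD of 11.** The observed SD varies, so the rules do not match exactly even here. In simulation at a true difference of -2, 2.6% of trials are significantly worse yet non-inferior, and 2.5% are non-significant yet fail the margin: about 5% in all. At -4 the total is about 7% (3.5% + 3.4%).

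**The case against.** The strongest reply is that this is a condensed article, and the comparison of a confidence limit with the margin may sit in a full protocol or SAP that is not shown. The analysis paragraph reads as a general default for all outcomes. It opens its sidedness rule with an exception clause, and the sample-size section does give a one-sided level and a margin. On that reading the sample-size section governs the primary comparison and the t-test covers the rest.

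This does not remove the problem. The exception clause has nothing to point to: the sample-size section gives its level and margin as sizing inputs and names no test or decision rule. The article does not merely leave the primary rule out. It fixes a rule for continuous outcomes, of which the primary endpoint is one, and that rule has the wrong null value. If an unseen SAP contains the margin test, the published text conflicts with it.

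Several parts of the reply do stand. Two-sidedness is not the defect, since a two-sided 95% CI from the same t model has the right one-sided 2.5% level once its lower limit is compared with -7. The planned data and sample size are adequate. The article nowhere says that P > 0.05 will be read as non-inferior, so the error rates at SD 13 to 16 describe what would happen under that reading and under those assumed SDs. The 20% power figure shows that the sample size does not serve the stated test; it is not a flaw in the sizing for non-inferiority.

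**Conclusion.** The concern holds and must be fixed. The design tests a deficit of 7 TSAT points, while the stated analysis tests a difference of zero, so the primary hypothesis has no valid decision rule in the text. The stated sample size gives 80.0% power for the margin test and 20.2% for the stated test at the planned 2-point difference.

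The practical size depends on the SD. At SD 11 with 77 per arm the rules disagree in about 5% of trials at the planned difference. If P > 0.05 were read as non-inferior, the error at a true 7-point deficit would rise from the planned 2.5% to between 8.7% and 23% for SDs of 13 to 16. At SD 9 the opposite error affects about 20% of trials at the planned difference. These figures assume normal data, equal SDs in the two arms, 77 evaluable per arm, 11 as an SD, and lower TSAT as the inferior direction.

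**What to change.** In Statistical analysis technique, add a rule for the primary endpoint: estimate the week-12 TSAT difference (iron polysaccharide complex minus iron sucrose) with a two-sided 95% CI, and conclude non-inferiority only if the lower limit is above -7 percentage points, which is a one-sided test at 2.5%. If a superiority claim is wanted, test it only after non-inferiority is met. Keep the two-sided P ≤ 0.05 rule for secondary comparisons, and state that P > 0.05 is not evidence of equivalence or non-inferiority.

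The cost is wording in the protocol and SAP. The sample size stays the same: with 77 per arm, SD 11 and a true difference of -2, power is 80.0%, and the error rate at a true difference of -7 is 2.5%.

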### Harms

Intravenous iron has a rare anaphylactic reaction, so we will conduct a small dose test before the first administration to ensure the safety of the participants. Safety endpoints are related directly to changes in laboratory safety indicators and incidence of adverse events between the treatment and control groups during follow-up. These endpoints will be listed according to the treatment received and recorded in detail. Participants will be followed up in detail; if any complications arise, appropriate treatment will be provided in accordance with current routine medical procedures.

### Ethics and dissemination

This clinical study has been approved by the Ethics Committee of Renji Hospital, School of Medicine, Shanghai Jiao Tong University (approval number: 2019-048). Other participating sub-centers must also obtain ethics committee approval documents prior to the start of clinical trials. The Good Clinical Practice (GCP) principles and guidelines shall be strictly followed during the test implementation [15]. At the same time, any problems related to the clinical trial must be reported to the ethics committee in a timely manner, such as changes in the trial protocol or participants’ information page, serious adverse events, termination or early termination of the clinical trial, etc. After the publication of study results, the study report will be published in a peer-reviewed journal and/or at a national or international conference. All researchers involved in the design, writing, and discussion of this clinical trial protocol are listed as the authors.

## Discussion

Anemia is one of the complications in participants on maintenance hemodialysis. The deficiency of hematopoietic iron is an important reason for this complication. Therefore, iron supplements are important to correct CKD-related anemia [16]. The commonly used iron preparations in clinical practice include intravenous and oral iron agents. Compared to oral iron, intravenous iron has the advantages of faster onset and better absorption. But it also has some limitations, such as inconvenient use of intravenous iron, which requires relatively high time and place of administration. At the same time, the health economics evaluation found that intravenous iron is more expensive than oral iron [17]. Accordingly, the intravenous iron agent is inferior to the oral iron agent in terms of the economic and convenience aspect of the treatment. At present, the main oral iron agent is divalent iron agent, which has some shortcomings such as low iron absorption rate, large gastrointestinal stimulation response, and relatively slow onset effect, which affect the therapeutic effect to some extent [18]. Iron polysaccharide complex, as an oral iron trivalent supplement, has the advantages of high iron content (46%) and gastrointestinal metabolism in the form of iron molecules without containing free iron ions.

There is little domestic clinical evidence of iron polysaccharide complex in the treatment of CKD-related anemia, so the application value and advantages of iron polysaccharide complex in the treatment of anemia in maintenance hemodialysis patients cannot be fully confirmed [19, 20]. Therefore, it is necessary to carry out further clinical trials to clarify the efficacy and safety of iron polysaccharide complex in correcting anemia in the maintenance of hemodialysis participants. In this study, intravenous injection of iron agent—iron sucrose will be used as the control group, and it is assumed that the efficacy and safety of iron polysaccharide complex in anemia and in maintenance hemodialysis participants will be non-inferior to that of iron sucrose injection. The purpose of this study is to increase the head-to-head data of oral iron compared with intravenous iron treatment and provide high-quality theoretical support for the treatment of CKD participants with CKD-related anemia. It is expected that this clinical trial will provide strong evidence as to the safety level and efficacy of iron polysaccharide complex in the treatment of anemia in maintenance hemodialysis participants. This study will provide a stronger evidence base for the development of guidelines in the treatment of CKD-related anemia and the establishment of efficacious and safe alternative treatments for managing iron deficiency anemia in chronic hemodialysis patients.

